## Abstract

**Background:**

The Nurse-Family Partnership (NFP) is an evidence-based home visiting program shown to improve maternal and child outcomes. Pro Kind is the first German adaptation of NFP, implemented between 2006 and 2012. While earlier evaluations demonstrated short- and medium-term benefits, no European trial has yet assessed long-term effects into adolescence.

**Objectives:**

This study protocol outlines the third phase of the Pro Kind randomized controlled trial (RCT), designed to evaluate the program’s effectiveness 14–16 years post-intervention. Primary aims are to assess adolescent and maternal outcomes related to mental health, parenting, risk behaviors, and life satisfaction, as well as potential long-term economic effects.

**Methods:**

The original RCT enrolled 755 pregnant women with psychosocial risk factors, randomly assigned to an intervention (*n* = 394) or control group (*n* = 361). The intervention comprised structured home visits from midwives or tandem teams (midwife + social worker) from pregnancy until the child’s second birthday. The 15-year follow-up combines self-report data (via online interviews and questionnaires) and administrative records on employment, social benefits, and criminal justice involvement. Discussion: This study represents the first long-term follow-up of an NFP adaptation in Europe. While U.S. trials of NFP provide evidence of the program’s effectiveness, these results cannot be generalized to European welfare contexts. This underscores the need for long-term evaluations of NFP adaptations in Europe to generate evidence that can inform policy and ensure evidence-based decision making.

## Introduction

Sustained Nurse Home Visiting programs (SNHVs) are considered one of the most thoroughly evaluated preventive approaches in Western industrialized nations to support socioeconomically disadvantaged families and to reduce health and developmental inequalities among children (1). These programs involve long-term (up to three years) repeated and regular home visits by trained family visitors (usually registered nurses, midwives, or social workers). Home visits typically begin during pregnancy and are continued postnatally. The Nurse-Family Partnership program (NFP) (2), developed in the 1970s by David Olds, is regarded as a prototypical example of SNHVs. The theoretical framework of the program is based on self-efficacy theory (3), human ecology (4), and attachment theory (5). NFP aims to improve prenatal health, strengthen parenting skills, and promote maternal life-course development in terms of education and employment. It comprises up to 64 home visits from pregnancy (preferably < 29 weeks of gestation) until the child's second birthday, conducted by specially trained and certified registered nurses. Since its development in the 1970s, NFP has been evaluated in the United States in several large-scale randomized controlled trials (RCTs).

The first RCT was conducted in the late 1970s in Elmira, a small town in the rural Chemung County in the Southern Tier region of New York State, with an initial sample of *N* = 400 mothers (Elmira Trial, 1978–1980) (6). For the subsequent comparative analysis, the NFP intervention group (IG: *n* = 116, nurse home visits from pregnancy until age 2) was compared with a composite control group (CG: *n* = 184, developmental screenings and, in some cases, transportation for prenatal appointments). The study primarily targeted young, first-time mothers with low educational attainment and low income. The home visits focused particularly on improving prenatal health (e.g., reducing smoking and substance use, promoting healthy nutrition), strengthening parenting skills (especially responsive caregiving and safe home environments), and fostering maternal self-efficacy and future planning, (e.g., continuing education, entering employment, preventing unplanned subsequent pregnancies). On average, approximately nine prenatal home visits (range: 0–16) and about 23 postnatal home visits (range: 0–59) were conducted during the first two years after birth, with a frequency of weekly visits during the first four weeks postpartum, followed by biweekly visits until the 21st month, and thereafter monthly visits [see (7)]. For the Elmira Trial, follow-up studies are now available up to 17 years after completion of the intervention [19-year follow-up (19yrs-fu)] (7).

The second RCT was conducted in Memphis, Tennessee, in an urban setting with a high poverty rate (Memphis Trial, 1990–1991) (8). The target group consisted predominantly of African American, unmarried, first-time mothers with low educational attainment and limited employment opportunities. A total of *N* = 1.139 mothers were enrolled in the study. For subsequent comparative analyses, the NFP condition (*n* = 228) was compared with a control condition (*n* = 515) similar to that used in the Elmira Trial. The program structure followed the model tested in Elmira but incorporated a stronger focus on health promotion in contexts of urban poverty. On average, approximately seven prenatal home visits (range: 0–18) and about 26 postnatal home visits (range: 0–71) were conducted during the first two years after birth (8). In addition to improving prenatal health, particular emphasis was placed on preventing substance abuse and enhancing socioeconomic prospects through education and employment planning [see (8)]. Follow-up assessments extend to child age 18 years (9). Furthermore, data on maternal and child mortality are available for a 20-year follow-up (10).

In the third trial in Denver, Colorado (Denver Trial, 1994–1995) (11), NFP was examined in a multi-ethnic urban setting. The multi-ethnic sample (46% Mexican American, 35% white non-Hispanic, 15% African American, 4% other) comprised first-time mothers with multiple psychosocial risk factors (including low income, single-parent status, and low educational attainment). The intervention structure followed the standard NFP protocol, with home visits delivered either by registered nurses (*n* = 235) or by paraprofessionals (*n* = 245). Both groups were compared with a control condition comprising *n* = 255 mothers. On average, registered nurses conducted approximately seven (range: 0–17) prenatal home visits and about 21 (range: 0–71) postnatal home visits from birth until the child's second birthday. Paraprofessionals conducted about six (range: 0–21) prenatal and approximately 17 (range: 0–78) postnatal visits (12). For the Denver Trial, follow-up studies are available up to the 9 years after the initial trial [9-year follow-up (9yrs-fu)] (13). Overall, the three RCTs demonstrate diverse and, in some cases, long-term intervention effects across different developmental domains. At the prenatal level, findings include a reduction in nicotine consumption during pregnancy [Elmira (14), Denver (11)], increased birth weight for boys [Memphis (15)], lower incidence of hypertensive pregnancy disorders [Elmira + Memphis, pooled (16)], fewer preterm births among very young mothers [14–16 years, Elmira (17)], and improved breastfeeding behavior [Elmira + Memphis (16)]. With regard to child health and developmental domains, improvements were observed in maternal parenting behavior during childhood and adolescence [Elmira: 1–2yrs-fu (14), Memphis: 6yrs-fu (15)], reduced rates of domestic violence, child abuse, and neglect [Elmira: 4–15yrs-fu (18), Memphis: 2–3yrs-fu (15, 19), Denver: 4yrs-fu, (20)], as well as lower rates of injury-related hospital visits [Elmira: 2yrs-fu (21), Memphis: 6yrs-fu, (20)]. In medium terms, improvements were also observed in attention-related abilities [Denver: 2–6yrs-fu, (13)], cognitive abilities [Elmira: 3–4yrs-fu (14); Memphis: girls: 6yrs-fu, boys: 6–12yrs-fu (15, 22); Denver: 4yrs-fu, (20)] and language skills [Denver: 2–6yrs-fu (13, 20)] in children, as well as lower prevalence rates of emotional problems and behavioral difficulties [Memphis: 6yrs-fu (15, 22), Denver: 6–9yrs-fu (13)]. Long-term follow-ups into late adolescence provide evidence of sustained effects such as lower crime rates and convictions [Elmira: 11–19yrs-fu (7), Memphis: girls: 18yrs-fu, (9)], improved academic performance [Memphis: 12–18yrs-fu (9, 23)], lower rates of adolescent substance use [Elmira: 12–15yrs-fu (16, 24), Memphis: 12yrs-fu (23)], and fewer teenage pregnancies among girls [Elmira: 19yrs-fu (7)]. Analyses from the Memphis Trial also indicate a long-term effect (20yrs-fu) of lower child mortality among NFP children compared to the control group (10). Mothers likewise benefited from the intervention in the form of fewer closely spaced pregnancies (within 24 months) and fewer abortions within 48 months postpartum (All Trials 16). Overall, NFP mothers reported lower rates of subsequent births [Elmira: 15yrs-fu (18), Memphis: 9yrs-fu (25), Denver: 4yrs-fu (20)]. In addition, NFP mothers showed higher labor force participation and reduced dependence on welfare benefits [Elmira: 4–15yrs-fu (18, 26), Memphis: 12yrs-fu (27)] as well as improvements in mental health [Memphis: 2–6yrs-fu (15)]. Furthermore, there were fewer maternal arrests [Elmira: 4–15yrs-fu (18)], fewer impairments due to alcohol and drug use [Elmira: 4–15yrs-fu (18)], and a reduced maternal mortality rate [Memphis: 20yrs-fu (10)].

In addition to the three original U.S. NFP studies (Elmira, Memphis, Denver), a recent cluster-randomized controlled trial (CRCT) was conducted to examine the scalability and implementation of NFP within the U.S. Medicaid system in South Carolina [2016–2020, *N* = 5.670 Medicaid-eligible mothers (28)]. The target group comprised first-time mothers eligible for Medicaid who often face multiple stressors such as poverty, limited access to health services, and unstable living conditions. The program structure followed the NFP standard (home visits by nurses from pregnancy until the child's second birthday; prenatal: 9 visits median, 18 mean) but was more strongly integrated into public service structures and supplemented with components to improve birth outcomes (e.g., prevention of preterm birth) and to reduce hospitalizations. The focus was on preventive health, parenting competence, and life planning, with particular attention to feasibility in large-scale state welfare-programs. The results to date (follow-up assessments are planned up to child age nine years) showed no significant effects on the primary birth outcomes [e.g., preterm birth, low birth weight, small for gestational age, perinatal mortality (28), birth intervals (1yr-fu) (29); or child mortality, severe injuries, and indicators of child abuse and neglect (2yrs-fu) (30)].

In addition, two further U.S. RCTs have been conducted on the SNHV program Minding the Baby (MtB), with partially long follow-up assessments [phase 1: 3–5yrs-fu, 2002–2005, *N* = 105 mothers at risk of adversity (31, 32); phase 2: 8yrs-fu, 2008–2011, *N* = 124 mothers at risk of adversity (33, 34)]. MtB was developed at Yale University in the early 2000s and targets first-time mothers and mothers aged 14–25 years (32, 35). Home visits usually begin during pregnancy and continue until the child's second birthday. Unlike NFP, home visits are conducted in a tandem model by advanced practice nurses and clinical social workers. The program focuses on strengthening the attachment relationship, promoting parental sensitivity and reflective functioning, and supporting the child's healthy emotional and cognitive development. The U.S. MtB studies have shown that children were more likely to have secure attachment and less likely to have disorganized attachment (31, 33) and, in infancy, exhibited fewer interaction problems (among adolescent mothers, 32). Additionally, MtB families were more likely to be fully vaccinated, young mothers were less likely to have a subsequent child after their first birth, and there were fewer child protection reports (31). In later follow-ups (3–5yrs-fu), lower levels of externalizing behavior problems (32), lower obesity rates (35), fewer general behavior problems were found. In [8yrs-fu] more frequent supportive parenting practices were found (34).

In addition to these U.S. trials, various international and high-quality evaluations (i.e., RCTs) of SNHVs have been conducted in countries with universal healthcare systems. These include international adaptations of NFP from the Netherlands [VoorZorg, 2yrs-fu, 2007–2009, *N* = 460 young [<25 years], first-time mothers with low socioeconomic status [SES] plus at least one additional risk factor (36, 37)], England [Building Blocks [BB], 7yrs-fu, 2010–2013, *N* = 1.645 teenage [<20 years] mothers with low SES (38, 39)], Germany [ProKind, 7yrs-fu, 2006–2010, *N* = 755 first-time mothers with low SES plus at least one risk factor (40–42)], and Canada (British Columbia Healthy Connections Project [BCHCP], 2yrs-fu, 2013–2016, *N* = 739 first-time mothers with low SES (43)], as well as adaptations of MtB from the UK [2yrs-fu, *N* = 148 young [<25 years] mothers (44)], and Denmark [2yrs-fu, 2018–2022, *N* = 256 young [<25 years] mothers (45)]. Furthermore, two additional RCTs are available for the Australian right@home (AUS) program [6yrs-fu, 2013–2014, *N* = 722 mothers with at least two risk factors (46, 47)] and its precursor, the Maternal Early Childhood Sustained Home-visiting (MECSH) program [2yrs-fu, 2005–2008, *N* = 208 mothers with at least one risk factor (48)]. Similar to NFP, home visits in these programs are delivered by registered nurses and extend from pregnancy until the child's second birthday but include additional modules to promote language and literacy development [see (49, 50)].

While SNHV studies conducted in universal healthcare contexts have reported some positive effects regarding birth and pregnancy outcomes [smoking: VoorZorg (51)] as well as positive medium-term outcomes (0–4yrs) for mothers [e.g., parental responsiveness: ProKind (52), MECSH (53), right@home AUS (49); parental self-efficacy: MECSH (53), ProKind (54), right@home AUS (49); breastfeeding: BB (55), VoorZorg (51), MECSH (56); postpartum health: MECSH (56), right@home AUS (49); home learning environment: ProKind (57), right@home AUS (46), VoorZorg (37)], and children [e.g., cognitive and psychomotor development: BB (55), ProKind (57); language: BB (55), right@home AUS (49); behavioral difficulties and emotional problems: MtB UK (58), VoorZorg (37)].

To date only three of these studies have provided extensive long-term (>6 yrs) evaluations. First, the BB study in England (39) linked educational, health and social administrative data up to age seven and reported modest benefits in reading (key stage 1), but no consistent effects across other educational (writing, mathematics, scientific understanding), health (e.g., use of emergency departments due to injuries or ingestion) or child protection outcomes (e.g., reports to social services and official designations as “Child in Need”). Second, the 6yrs-fu of the Australian right@home program (59) reported improvements in children's socio emotional adjustment, social competence and executive functioning, alongside higher maternal wellbeing and warmer parenting, although no significant effects were found for children's general health, school achievement, emotional abuse or maternal distress, general health or self-efficacy. Compared to these studies, the German ProKind trial provides a comparable but slightly longer observation window. At the 7yrs-fu, the program was associated with significant reductions in internalizing and externalizing child behavior, higher maternal wellbeing, and decreases in abusive and neglectful parenting [see (41, 42)].

Building on this evidence, the present paper introduces the protocol for the long-term follow-up of ProKind (approx. 15yrs-fu). This study will be the first to examine whether the intervention effects of an SNHV program in a European welfare state persist into adolescence, thereby extending the existing international evidence beyond early and middle childhood and into a developmental stage marked by heightened social, emotional, and behavioral challenges (60).

## The German adaption of NFP – the ProKind study

In Germany, the concept of early intervention (“Frühe Hilfen”) was introduced in the 1970s as part of healthcare and child welfare programs [Nationales Zentrum Frühe Hilfen (NZFH)]. Despite the development of numerous initiatives, there was a lack of comprehensive evaluation research (61). To address this gap, the Federal Ministry for Family Affairs, Senior Citizens, Women and Youth (BMFSFJ) launched the “Early Support and Social Early Warning Systems” program in 2006. These efforts led to increased attention and conceptual differentiation of early support measures in Germany, particularly regarding prevention and child protection. One such initiative is the ProKind study, a multicenter RCT adapting the NFP program for Germany (40). The intervention within the ProKind study was conducted between 2006 and 2012 in the German federal states of Bremen (a city-state in northern Germany known for its urban environment and relatively high levels of social disparities), Lower Saxony (a largely rural state with pockets of urbanization and a diverse socio-economic landscape), and Saxony (an eastern state characterized by its post-reunification socio-economic challenges and unique demographic structure).

## Sample at baseline and randomizations procedure

At the time of baseline data collection (2008–2009), women in the 12th to a maximum of the 28th gestational week were recruited based on the following inclusion criteria: (a) an ongoing pregnancy (<28 weeks), (b) at least one financial risk factor [e.g., receipt of unemployment benefits (ALG II), debt], (c) at least one additional social or personal stress factor (e.g., being underage, lack of a school diploma, personal experiences of abuse or neglect) and (d) at least basic knowledge of the German language to enable communication with the German-speaking family companions (≙ A1–A2 language level). Participants were recruited through various intermediaries, including gynecologists, midwives, youth welfare offices, psychosocial counseling centers, and employment agencies. In total, *N* = 1.157 interested pregnant women registered to participate in the project. Of these, *n* = 263 did not meet the inclusion criteria, and *n* = 139 declined participation after receiving detailed information about the project. The final sample of *N* = 755 women was randomly assigned to an intervention group (IG, *n* = 394) or a control group (CG, *n* = 361) using Efron's Biased Coin Design (62), stratified by municipality (urban vs. rural), age (≤18 vs. >18 years), and maternal nationality (German vs. non-German). The women were, on average, 21 years old at the start of the project; approximately 88% were unmarried (about 28% were single parents), and about 12% had a migration background. Only about 18% reported that the current pregnancy was unwanted. The CG did not receive any study-related interventions but had access to the regular services of the German healthcare system (*treatment as usual*, TAU). This includes the statutory right to midwifery care during pregnancy, childbirth, and the postpartum period, as enshrined in the German Midwifery Act (HebG) and the Midwifery Training and Examination Regulation (HebAPrV).

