Consistent with the second phase of the ProKind study, information is collected regarding prior employment, periods of unemployment, welfare receipt, participation in qualification programs during unemployment, and employment details from the Technical Data Center (FDZ) of the IAB in Nuremberg, which is part of the German Federal Employment Agency. Participants had the option to provide self-reported data but withhold permission for researchers to access administrative data. Furthermore, the data linkage with the EMA allows access to official records on mortality of both children and mothers as well as on further births of the participating mothers and their children. Regular inquiries are made to the Federal Central Criminal Register (Bundeszentralregister, BZR). This register records criminal convictions by German courts, certain decisions by administrative authorities, notes on incapacity to be held criminally responsible, and special judicial determinations, as well as subsequent decisions and facts related to these entries. When the relevant conditions are met, foreign convictions of German nationals or individuals born or residing in Germany are also entered into the register. An anonymized report for scientific research purposes is unrestrictedly possible.

Power analyses indicated that with a one-sided test at *α* = .05 and statistical power of 1–*β* = .80, the trial is adequately powered to detect small effects. Calculations were based on the original allocation proportions of the study (*n* = 394 in the IG and *n* = 361 in the CG). Three scenarios were considered. Scenario 1 assumes administrative data with an expected re-engagement of 93% (*n* ≈ 700) which allows the detection of effects of at least ES = 0.19. Scenario 2 assumes a response rate of about 70% (*n* ≈ 530) as observed in the 7yrs-fu (41) which allows the detection of effects of at least ES = 0.22. Scenario 3 assumes a more conservative retention rate of 60% (*n* ≈ 450) which allows the detection of effects of at least ES = 0.23. According to Cohen (93), these values correspond to small effect sizes.

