## Data analysis

The primary and secondary analyses will be conducted on an intention-to-treat basis. We will standardize and recode all continuous outcomes such that positive values correspond to beneficial effects. The reported effect sizes (ESs) will be interpreted as group differences in standard deviations (SDs) of the CG. Confidence intervals (CIs) for the ESs will be obtained using bootstrap methods with 5,000 replications. One-sided tests (*p* < .05) will be conducted under the assumption that the intervention is not harmful.

Following the analytic strategy used in the 7yrs-fu of ProKind (41), as well as in recent evaluations of the trial (42, 71), to address missing observations from families who did not participate in the follow-up and to account for the imbalance in a few baseline risk factors (e.g., maternal aggression and mental health problems) between IG and CG, treatment effects will be estimated using augmented inverse probability weighting (AIPW) in combination with the “least absolute shrinkage and selection operator” (lasso) to select relevant control and weighting variables (107).

The AIPW technique assigns weights to observed cases based on the inverse of their probability of loss to follow-up estimated by logit functions, thereby mitigating potential selection bias caused by attrition. In a second step a linear weighted function with additional control variables is estimated. The variables used in the logit functions for the weighting and the control variables for the linear weighted function are selected by lasso, a machine learning algorithm. By weighting participants according to their inverse probability of remaining in the study, the analytic sample is reweighted to more closely resemble the original randomized population, thereby improving both internal validity and generalizability of the findings. Due to findings of the last program phase, all primary and secondary outcomes will be analyzed regarding any differential effects, while controlling for children's gender (41) and delivery model (42).

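### The 394:361 split is very unlikely under the stratified biased coin described unless the coin was weak or the strata were finer than stated; the allocation text needs correcting and the allocation units should be forced into the model

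*Protocol article*

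**What the plan says.** In the protocol article, the section on the baseline sample and randomisation procedure states the method as "using Efron's Biased Coin Design (62), stratified by municipality (urban vs. rural), age (≤18 vs. >18 years), and maternal nationality (German vs. non-German". It reports the outcome as "intervention group (IG, *n* = 394) or a control group (CG, *n* = 361". It gives no coin probability, no target ratio and no counts by stratum.

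The same section accounts for everyone before allocation: 1,157 women registered, and "n* = 263 did not meet the inclusion criteria, and *n* = 139 declined participation". Then "The final sample of *N* = 755 women was randomly assigned".

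In the section on procedure and re-engagement, the power paragraph adopts the realised split: "Calculations were based on the original allocation proportions of the study (*n* = 394 in the IG and *n* = 361 in the CG".

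The Data analysis section plans augmented inverse probability weighting (AIPW). Its stated reasons are missing follow-up and imbalance in a few baseline risk factors. The weights are described this way: "The AIPW technique assigns weights to observed cases based on the inverse of their probability of loss to follow-up estimated by logit functions". Lasso selects both the weighting variables and the control variables of the outcome model. The stratification factors are not named as fixed terms.

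**The concern.** A biased coin favours the smaller arm whenever a stratum is out of balance. With only 8 strata, the differences within strata stay small and so does their sum. A total difference of 33 does not look like the output of such a procedure, and no post-randomisation exclusion is available to explain it.

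The analysis takes its authority from the randomisation. Suppose the chance of intervention differed by municipality, stratum or recruitment period. The arms would then differ in their mix of these by design. The weights described address follow-up only, and lasso may or may not select the terms that would correct the rest. The recruitment period is also unclear: the randomisation section puts baseline data collection in 2008–2009, while the section on the German adaptation dates the intervention 2006–2012. A reader therefore cannot tell from the article whether the procedure changed over time.

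**Working it through.** **Flow.** 1,157 − 263 − 139 = 755, and 394 + 361 = 755. The counts close, so nobody was removed after allocation to create the gap. The difference is 394 − 361 = 33, and the intervention share is 394/755 = 52.2%.

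**Inputs from the article.** N = 755; strata 2 × 2 × 2 = 8; no unequal target stated, so 1:1 is taken.

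**Assumptions.** The coin probability p is varied, because the article does not give it. Stratum sizes are either equal (94 or 95 women each) or unequal. The unequal case uses 12% non-German (the stated 12% with a migration background serves as a proxy), 27% aged 18 or under and 65% urban; the last two shares are assumed.

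**Method.** Within a stratum let D be intervention minus control. The next woman goes to intervention with probability 1/2 if D = 0, p if D < 0, and 1 − p if D > 0. The exact distribution of D after all women in the stratum follows by recursion. The distributions are convolved over strata, and the two-sided chance of a total difference of 33 or more is read off.

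**Eight strata** (ranges cover equal and unequal sizes):

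| Coin p | SD of total difference | 33 / SD | Chance of 33 or more |
|---|---|---|---|
| 0.75 | 3.9–4.0 | above 8 | 2–3 × 10⁻¹⁰ |
| 2/3 | 5.8–6.0 | 5.5–5.7 | 2–6 × 10⁻⁶ |
| 0.60 | 8.8–9.8 | 3.4–3.7 | 0.0009–0.0023 |
| 0.55 | 14.2–16.2 | 2.0–2.3 | 0.027–0.049 |
| 0.52 | 20.7–22.3 | 1.5–1.6 | 0.12–0.15 |
| 0.50 (simple 1:1) | √755 = 27.5 | 1.2 | 0.24 |

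**More strata, coin 2/3.** This covers the possibility that each municipality was its own unit, crossed with age and nationality (four cells per municipality).

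| Strata | Municipalities | Chance, equal sizes | Chance, unequal sizes |
|---|---|---|---|
| 24 | 6 | 0.002 | 0.0008 |
| 40 | 10 | 0.012 | 0.004–0.005 |
| 60 | 15 | 0.029 | 0.012–0.014 |
| 80 | 20 | 0.047 | 0.024–0.027 |

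The small ranges in the last column reflect how fractional stratum sizes are rounded.

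The split therefore becomes unremarkable in two ways that keep a 1:1 target. The coin may have been close to fair, in which case the design did little balancing. Or the strata may have been far more numerous than the three binary factors imply. An unequal or changing target ratio, or overriding of the coin, would also produce it.

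**The case against.** The strongest reply is that the result turns on a parameter that the article does not state. At a coin of 0.55 the split is only mildly unusual, and at 0.52 it is ordinary. A second reply is that the bracket after municipality may be condensed wording for stratification by individual municipality in a multicentre trial. Coin bias and exact units of a randomisation completed long ago are details that a follow-up article may leave to fuller documents. Both replies stand as possible explanations, but neither leaves the text sound. Finer strata would mean that the stated factors are wrong, and a near-fair coin would mean that the description misleads. The point is the misfit between stated method and stated result, not the missing detail.

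Stronger readings are tempting, and the article does not support them.

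- **That the split is impossible, so another allocation was used.** This needs a coin of about 0.60 or more and exactly 8 strata. The coin is unknown.
- **That the treatment effect is confounded.** Nothing shows that the chance of intervention varied by site, stratum or period. A constant ratio near 52:48 would not confound. The acknowledged imbalance in maternal aggression and mental health problems concerns variables that were not stratification factors, so it says nothing about the coin, and the same sentence gives it as a reason for choosing AIPW.
- **That the plan assumes equal allocation chances in every stratum.** It does not say so. It describes weights for follow-up and leaves covariates to lasso.
- **That the bias can be sized.** The article gives neither the part of the sample in which an excess arose nor how outcomes differed there.
- **That the power paragraph contradicts the randomisation section.** It uses the realised counts and states no target.

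**Conclusion.** The point holds in limited form. With 8 strata, a 1:1 target and a coin of about 0.60 or stronger, a difference of 33 in 755 is very unlikely: about 0.001 to 0.002 at 0.60 and 2 to 6 in a million at 2/3. With a coin of 0.55, or with 60 to 80 strata at 2/3, the chance is of the order of 0.01 to 0.05. The allocation description is therefore wrong or incomplete, and the article does not allow a choice between the explanations. Bias in the treatment effect is possible but not shown, and no size can be given for it. What can be said of the analysis is narrower: entry of the variables by which women were allocated depends on lasso selection, and this should not be left open when the allocation mechanism itself is in doubt.

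**What to change.** 1. Check the allocation records. Correct the randomisation section to state the coin probability, the target ratio and any change over time, and the actual stratification units.
2. In the Data analysis section, state that the actual allocation units and stratification factors enter both the weighting model and the outcome model unpenalised, with lasso choosing only among the remaining covariates. These are municipality or urban/rural (whichever was used), age 18 or under, and nationality. Add enrolment period if the ratio changed.
3. If the records show that allocation probabilities varied, include the known probabilities in the AIPW weights.

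Re-randomisation p-values that replay the actual algorithm are an optional sensitivity analysis.

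The cost is a look-up in existing records, a text correction and a few model terms. No new data are needed. The downside is a few degrees of freedom, and more of them if individual municipalities turn out to be the units.
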